### Statistical analysis plan

The field and laboratory data will be merged, harmonised, cleaned and analysed with STATA® version 18.1 SE (Stata Corp., College Station, TX, USA). Descriptive statistics such as frequencies and proportions will be used to summarise the baseline parasitic parameters and socio‐demographical characteristics of the study participants by cluster arm. Data will be analysed using an ITT approach. The proportions of adverse events and the incidence (average number per participant) of reported adverse events will be compared between the study groups using the Chi‐squared test. Logistic regressions with robust standard errors will be used to estimate odds ratios and 95% confidence intervals. Wald tests will be used to assess the evidence of difference in odds between study groups, after controlling for baseline characteristics (sex, age group, weight and malaria and helminth infections' occurrence). Effect modification between intervention period and study groups will also be investigated using the Wald test. The geometric means of the *P. falciparum*, STH and schistosome intensities will be estimated and plotted before and after intervention periods. A univariable Poisson regression with robust standard error and Wald test will be used to compare the pre‐intervention parasites intensities across groups, and a multivariable Poisson regression including the pre‐intervention parasites intensities as a covariate, adjusting for other baseline characteristics described above, and Wald test will be used to compare the post‐intervention parasites intensities. The proportions of adverse events and the incidence (average number per participant) of reported adverse events will be compared between the study groups using the Chi‐squared test. All statistical tests will be two‐sided at a significance of *α* <0.05.

The economic analysis will have three parts:a detailed cost analysis of (a) the incremental financial and economic costs of implementing integrated treatment versus SMC alone; (b) modelling costs of delivery at scale; and (c) cost savings from cases of anaemia averted;a budget analysis that compares the net financial costs of delivery at scale minus cost savings from anaemia cases averted against the appropriate Ministry of Health budget to assess if the new intervention is affordable; anda CEA that uses a decision model approach to estimate the ICER of integrated SMC + anti‐helminthic treatment versus SMC alone, in terms of incremental economic costs per incremental measure of effect (DALY averted).

The impact of uncertainty and heterogeneity on results will be explored using deterministic and probabilistic sensitivity analyses to assess the robustness of ICERs to key model parameters (e.g., cost of drugs, effectiveness measures, time taken to deliver MDA in addition to SMC, etc.). The ICER per DALY averted will be compared against context‐appropriate willingness‐to‐pay thresholds [29, 30].

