### Sample size determination

We assumed that the mean Hb concentration in the SMC alone group will be 10.5 g/dL with a standard deviation of 1.5 g/dL [3]. Assuming an intra‐class correlation coefficient of 0.05, then 10 communities per cluster, a study of 60 children per community will have 80% power to detect an increase in mean Hb of 0.5 g/dL (to 11.0 g/dL) in the SMC plus anthelminthic group as statistically significant at 5% level. A minimum sample size of 1200 school‐age children (5–10 years) will be enrolled. This study will be implemented in three stages: pre‐intervention, intervention and post‐intervention. The pre‐intervention survey will be conducted to determine the prevalence of malaria‐helminth co‐infection in the study population.

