
##### Intervention stage

Given that the focus of this project is to evaluate the effectiveness of the integrated SMC‐MDA control programmes, the first day of starting the intervention stage (Day 0) will correspond to the day prior to the commencement of the first cycle of SMC in the study area. On Day 0, the communities will be randomised at community level into two clusters at 1:1 ratio to receive either combined SMC and anthelminthic drugs (intervention cluster) or SMC drugs only (control cluster). Given that 4‐aminoquinoline drugs are reported to have antagonistic pharmacological interactions with PZQ [23], the SMC partner drugs, AQ (a 4‐aminoquinoline derivative) and SP will not be administered with anthelminthic drugs (ALB and PZQ) on the same day in this study. Therefore, eligible children randomised into the intervention clusters will receive ALB and PZQ on Day 0 and those randomised into the control clusters will receive vitamin A and zinc supplement as control drugs on this day. On the following day, which corresponding to the start (Day 1) of the first SMC cycle, the children in the control and intervention clusters will receive SPAQ according to the WHO and Ghana SMC implementation guidelines. This will be followed on the second and third day of the SMC cycle with all study children in the two groups receiving AQ, in line with the SMC guidelines [5]. The study will administer AQ on Days 2 and 3 to the children in the presence of their parents/caregivers. Trained field workers will visit all enrolled children daily, irrespective of the study arms, at home starting from the evening of Day 0 till 3 days after completion of the first cycle of SMC course, using a purpose‐designed electronic diary card, to collect adverse drug reactions and adverse events such as vomiting, skin rash, body weakness, etc. Trained research assistants will visit each child 1 month after each round of SMC cycle to check that there are no severe reactions to the previous treatment and to give the next round of treatment (Table 1).

**TABLE 1 tmi14062-tbl-0001:** Schematic diagram of the study procedures for the effectiveness study.

SMC cycle	1					2, 3 and 4	End of malaria season (i.e., 1 month after completion of the last SMC cycle)
Timelines (days)	Pre‐intervention survey	Day 0	Day 1	Days 2 and 3	Days 4–6		Post‐intervention survey

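### Adverse events are compared by a chi-squared test with no allowance for community randomisation, and the same test is applied to a mean count, so false safety differences become more likely

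*Protocol article*

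**What the plan says.** In the protocol article, the Intervention stage section has communities "randomised at community level into two clusters at 1:1 ratio"; here the word cluster is used for a study arm. Sample size determination gives "then 10 communities per cluster" and "a study of 60 children per community", with an "intra‐class correlation coefficient of 0.05". That calculation is for mean haemoglobin. The section on sampling for the intervention stage speaks of schools rather than communities, but with the same 10 per arm and 60 children each.

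The Statistical analysis plan section names one test for two safety quantities. One is the proportion of adverse events; of the other, the section states that "incidence (average number per participant) of reported adverse events will be compared between the study groups using the Chi‐squared test". The sentence appears twice, and neither appearance mentions clustering. After the first, the section plans logistic regressions with robust standard errors and Wald tests adjusted for baseline characteristics, without naming an outcome or a clustering unit. All tests are two-sided at 5%.

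Endpoints lists solicited adverse events and drug-related reactions over six days as a secondary endpoint.

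**The concern.** The design allows for correlation within communities when it sets the sample size, but the named safety test does not. An ordinary chi-squared test on arm totals treats 1200 children as independent. If children in one community tend to have, or report, events alike, the variance is understated and the p-value is too small.

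The second problem is separate. The article defines incidence as an average number per participant, which is a mean count. A chi-squared test compares counts in categories. It can be made to compare event totals between arms, but it then assumes that events are independent and Poisson, which fails if some children contribute several events.

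At stake is a false signal of a difference, in either direction, on a secondary safety endpoint. The arms are meant to be compared on this: Study design gives control children vitamin A and zinc so that adverse-event reporting is objective.

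**Working it through.** **Inputs.** From Sample size determination: 10 communities per arm, 60 children each, ICC 0.05 (haemoglobin only), "standard deviation of 1.5 g/dL", and a design that "will have 80% power to detect an increase in mean Hb of 0.5 g/dL" at the 5% level. From Statistical analysis plan: two-sided tests and the chi-squared test. Assumed, because the article gives no figures: the ICC for adverse events, and the variance-to-mean ratio of events per child.

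**The plan's own figure.** Without clustering, n per arm = 2 × (1.960 + 0.842)² × 1.5² / 0.5² = 141.3, rounded up to 142. Design effect = 1 + (60 − 1) × 0.05 = 3.95. Then 142 × 3.95 = 560.9 per arm, and 560.9 / 60 = 9.35, rounded up to 10 communities, or 1200 children in all. Power at 10 × 60 per arm is 82.8% by the normal approximation and 78.4% by t with 18 degrees of freedom. These lie either side of the stated 80%, so the sample size does allow for clustering.

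**Chi-squared test on proportions.** With equal communities of 60, design effect D = 1 + 59 × ICC. True type I error of the nominal 5% test = 2 × [1 − Φ(1.96 / √D)]. Effective sample size per arm = 600 / D.

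| Assumed ICC for adverse events | D | 1.96/√D | Type I error | Effective n per arm |
|---|---|---|---|---|
| 0 | 1.00 | 1.96 | 5.0% | 600 |
| 0.005 | 1.295 | 1.72 | 8.5% | 463 |
| 0.01 | 1.59 | 1.55 | 12.0% | 377 |
| 0.02 | 2.18 | 1.33 | 18.4% | 275 |
| 0.05 | 3.95 | 0.99 | 32.4% | 152 |

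**Simulation check.** Beta-binomial data were simulated under no difference: 20 communities of 60, event risk 10% or 30%, 20,000 replicates per setting. The chi-squared test rejected in 11.4–11.8% of replicates at ICC 0.01, 18.6–18.9% at 0.02 and 31.9–33.1% at 0.05. A t-test on the 20 community proportions (18 degrees of freedom) rejected in 4.8–5.2% across ICC 0 to 0.05.

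**Chi-squared test on event totals.** With arm totals a and b, the statistic is (a − b)² / (a + b), which assumes variance equal to the mean. If the per-child variance-to-mean ratio is φ, type I error = 2 × [1 − Φ(1.96 / √φ)], even with no clustering:

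- φ = 1.5: 11.0% (simulated 11.0–11.7%)
- φ = 2: 16.6% (simulated 16.3–17.6%)
- φ = 3: 25.8% (simulated 24.6%)

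Clustering would add to this.

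**The case against.** The strongest reply is that the adjacent logistic regression with robust standard errors is the real between-arm analysis and may cover adverse events. It may be so intended. But the sentence names no outcome, does not say that the errors are clustered on community, and does not replace the chi-squared test, which is stated again at the end of the section. A logistic model would in any case not analyse a mean number of events.

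A second reply is that an article condenses the full plan. That accounts for missing detail; here an unsuitable test is named.

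Several other objections stand, and they limit the point:

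- A reader might take 32% as the error at the planned ICC. The 0.05 belongs to haemoglobin, and no ICC is planned for adverse events.
- A reader might infer that safety confidence intervals will be about half their proper width. The chi-squared test gives a p-value, and no interval based on it is planned.
- A reader might see this comparison as the basis for calling the package safe. The Introduction and Discussion credit safety to the earlier trial, and Ethical considerations assigns oversight of participant safety to an independent board.
- Field workers visit children at home, but the article does not say they are assigned by community. Within-community correlation is plausible, not documented.
- A chi-squared comparison of event totals is valid if counts are Poisson and independent.

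**Conclusion.** The method is wrong as written. For proportions, the test has its nominal 5% level only if the within-community correlation of adverse events is zero. Over assumed ICCs of 0.005 to 0.05 the true level is about 8.5% to 32%; the range is illustrative because the article gives no value. For the average number per participant, the test does not match the quantity. Used on event totals with assumed variance-to-mean ratios of 1.5 to 3, its level would be about 11% to 26% before any clustering. The proportion figures also assume equal communities of 60 and a chi-squared test computed on individual children, which is the ordinary meaning of the unqualified wording.

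The consequence is more false differences on one secondary endpoint. The documents do not support a wider reading that harms would be concealed or that the primary haemoglobin result is invalid; this sentence does not govern that analysis. It should be fixed before the data are analysed, but it is not a must-fix.

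**What to change.** Replace both chi-squared sentences.

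- **Proportion of children with an event:** compare community-level proportions by a t-test with 18 degrees of freedom, or use a mixed or GEE logistic model clustered on community with a small-sample correction for 20 clusters.
- **Events per child:** use a Poisson or negative binomial model with the same clustering and correction, reported as a rate ratio with a 95% confidence interval.
- **Adjacent logistic regression sentence:** name the outcomes it covers and state that the robust standard errors are clustered on community.

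The cost is a change of wording. No data collection or sample size changes. The p-values will generally be larger, and true differences in adverse events will be somewhat harder to declare significant, because the effective sample is smaller than 600 per arm whenever the correlation is positive.

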#### Sampling for the intervention stage of the trial

There will be two study arms in the intervention phase of this trial—intervention and control arms. Ten schools within Pru East communities will be randomised to the intervention arm and another 10 schools will be randomised to the control arm. As calculated above, a minimum of 60 children who satisfy all eligibility criteria will be enrolled sequentially in each of the 10 schools randomised into the intervention and control arm, respectively. To identify these children, we will undertake a census of all children aged 5–10 years in the communities selected for the intervention stage of the trial. Subsequently, we will use a sampling frame for random sampling from the census list to enrol the required number of children into each study arm. We will keep a reserve list of potentially eligible children in case of any refusals from the sampling list.

Data collection for the cost‐effectiveness analyses will involve semi‐structured interviews with key informants from the regional and district education and health offices, using purposive sampling to select health facility personnel, community health workers (CHWs) and school teachers involved in the delivery of SMC with or without MDA for helminths. Approximately 6–12 interviews are anticipated at the regional and district level, up to 10 with health facility personnel, 10–15 with CHWs and 10–20 with school teachers. Key informants will be chosen to reflect maximum expected variation across the study area, for example, a mix of urban and rural communities, distance from the district centre, etc. This flexible and purposive approach to sampling is a standard and important feature of economic evaluations.

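### The stated regressions and chi-squared tests do not name the randomised community as the cluster, so the nominal 5% level is missed, modestly or severely depending on what robust means

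*Protocol article*

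**What the plan says.** **Design.** Under Intervention stage, "the communities will be randomised at community level into two clusters at 1:1 ratio". The section on sampling for the intervention stage calls the units schools: "Ten schools within Pru East communities will be randomised to the intervention arm and another 10 schools will be randomised to the control arm". Either way there are 20 randomised units.

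**Sample size.** Sample size determination allows for clustering: "Assuming an intra‐class correlation coefficient of 0.05, then 10 communities per cluster", with 60 children in each community.

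**Analysis.** The Statistical analysis plan section gives four kinds of between-arm inference, all two-sided at 0.05:

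- Binary outcomes: "Logistic regressions with robust standard errors will be used to estimate odds ratios and 95% confidence intervals", with Wald tests after adjustment for baseline characteristics.
- Pre-intervention parasite intensities: "A univariable Poisson regression with robust standard error and Wald test".
- Post-intervention intensities: a multivariable Poisson model with a Wald test. No type of standard error is given.
- Adverse events: chi-squared tests between the study groups, stated twice.

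The section names no clustering variable, random effect, GEE or community-level summary, and no correction for the small number of communities.

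**The concern.** The sample size treats children in one community as correlated, but the analysis as worded does not say that it does. An analyst who asks for robust standard errors without naming a cluster variable gets errors that allow for unequal variances and still treat the 1200 children as independent. The chi-squared tests make that assumption outright. If instead the errors are clustered on community, a Wald test against the normal distribution is still somewhat too liberal with only 20 communities.

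The outcomes at stake are secondary: prevalence of anaemia, of *P. falciparum* infection, of helminth infection and of co-infection, post-intervention intensities, and adverse events. Anaemia cases averted also feed the DALY calculation. Effectiveness measures are among the parameters varied in the economic sensitivity analyses, so overstated precision could carry over to the cost-effectiveness results.

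**Working it through.** **Inputs from the article.** 10 communities per arm, 60 children each, ICC 0.05, "10.5 g/dL with a standard deviation of 1.5 g/dL", difference 0.5 g/dL, 80% power, two-sided 5%.

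**1. Reproduce the sample size.**
- Without clustering, 142 children per arm are needed.
- Design effect = 1 + (60 − 1) × 0.05 = 3.95.
- 142 × 3.95 = 560.9 per arm; 560.9 / 60 = 9.35, rounded up to 10 communities per arm. 2 × 10 × 60 = 1200, as stated.
- Power at that size is 82.8% by the normal approximation and 78.4% with a t reference on 18 degrees of freedom (df), either side of the stated 80%.

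The planned size therefore already includes the design effect of 3.95.

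**2. Reading A: robust means heteroscedasticity-only.** Standard errors are too small by √DE, where DE is the design effect. The true type I error of a nominal 5% test is 2 × [1 − Φ(1.96 / √DE)]. The ICC for binary outcomes is an assumption, so a range is shown.

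| Assumed ICC | DE | √DE | 1.96/√DE | Type I error | Coverage of 95% CI |
|---|---|---|---|---|---|
| 0.01 | 1.59 | 1.26 | 1.55 | 12% | 88% |
| 0.02 | 2.18 | 1.48 | 1.33 | 18% | 82% |
| 0.05 | 3.95 | 1.99 | 0.99 | 32% | 68% |
| 0.10 | 6.90 | 2.63 | 0.75 | 46% | 54% |

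The same formula applies approximately to a child-level chi-squared test of the proportion with an adverse event, at whatever ICC that outcome has.

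**3. Reading B: robust means clustered on community, with a normal-reference Wald test.** Using the critical value 1.960 where t on 18 df requires 2.101 gives a type I error of 6.6% from the reference distribution alone.

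**4. Simulation of both readings.** Null logistic models were fitted to 20 communities of 60 children, with beta-binomial outcomes at prevalence 0.3 or 0.5, with and without covariates, 2000 runs per setting. The Monte Carlo standard error near 7% is √(0.07 × 0.93 / 2000) = 0.6 percentage points.

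| Method | ICC 0.01 | ICC 0.05 |
|---|---|---|
| Robust, unclustered, z | 10.7–13.2% | 31.5–33.3% |
| Clustered on community, z | 6.6–7.6% | 7.1–7.9% |
| Clustered on community, t(18) | 5.1–5.8% | 5.1–6.0% |

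A separate set of 4000-run simulations gave 19%, 32–33% and 45% for unclustered errors at ICC 0.02, 0.05 and 0.10. It gave 7–9% for clustered errors with z, and 4.4–5.6% for a community-level t-test on 18 df.

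**5. Width of the intervals.** Moving from reading B to t(18) widens an interval by 2.101 / 1.960 = 1.07. Moving from reading A at ICC 0.05 widens it by 1.99 × 1.07 = 2.13.

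**The case against.** The strongest reply is that robust may be shorthand for cluster-robust. The authors sized the trial with an ICC, and in a logistic model a sandwich estimator has little purpose other than handling within-cluster correlation. On that reading the large figures fall away and a modest excess over 5% remains. The article is also a condensed account, and the choice of small-sample correction is often left to a full analysis plan.

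Much of this stands. A reader might infer that the trial will certainly be analysed as 1200 independent children; the text does not say so, and the 32% is conditional. Three other tempting extensions also go too far:

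- *That the primary endpoint is affected.* The section names no model for change in haemoglobin, so nothing can be concluded about it.
- *That the univariable Poisson model shows efficacy ratios to be at fault.* It compares intensities before the intervention. The post-intervention model has no stated type of standard error, and the robust wording cannot simply be carried over to it.
- *That ICC 0.05 holds for every outcome.* It is given for haemoglobin only. Adjustment for baseline infection might also absorb some between-community variation, which would move the error towards the lower rows of the assumed range.

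The reply does not remove the point. The section names its models, tests, covariates and significance level, so this is a stated method and not just an unreported detail. Its chi-squared tests have no reading that allows for clustering, which weakens the case that clustering was silently intended elsewhere. Nor does the article's vocabulary settle it, since it often uses cluster for the arm, as in "10 communities per cluster, a study of 60 children per community".

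**Conclusion.** The point holds in conditional form. As written, none of the named analyses is stated to account for the randomised community, although the sample size does. For secondary binary outcomes the nominal 5% is missed on both readings of robust: about 32% if the errors are unclustered at ICC 0.05 (12% to 46% for ICC 0.01 to 0.10), and about 7 to 8% if they are clustered on community with a normal-reference Wald test. The adverse event tests ignore clustering on any reading. For post-intervention intensities the method is not fixed well enough to attach a figure.

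These sizes assume equal communities of 60 with no dropout, and ICCs for non-haemoglobin outcomes that the article does not give. The two readings imply intervals that differ about twofold in width at ICC 0.05, so the wording should be settled before the between-arm analysis.

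**What to change.** State in the Statistical analysis plan section that every between-arm comparison, including adverse events and post-intervention intensities, takes the randomised community as the cluster and uses a small-sample correction. Suitable options are:

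- cluster-robust or bias-corrected sandwich errors with a t reference on 18 df; or
- a community-level summary t-test on 18 df.

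This wording would replace the unqualified robust and Wald wording and both statements of the chi-squared test, and would give the post-intervention Poisson model a stated type of standard error. Use one name for the randomised unit, since the article calls it a community in some places and a school in another.

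The cost is wider, correctly sized confidence intervals. No new data are needed. If the haemoglobin comparison is held to the same standard, its power at the planned size is 78.4%, close to the stated 80%.

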To maximise the impact of our findings, we will evaluate the effectiveness of the integrated SMC and MDA of anthelminthic drugs on the prevalence of anaemia and malaria‐helminth co‐infection in a larger paediatric population than was included in the pilot trial. This study will test the hypothesis that haemoglobin (Hb) concentration will be higher in the combined SMC‐MDA group than in the SMC alone group. Given that the analysis of the economic and financial costs of delivering the integrated model will be needed to inform resource allocations, allow comparison with alternative interventions, and inform deployment of the approach, if successful, we will also evaluate the costs and cost‐effectiveness of the integrated delivery model for SMC‐MDA among the study children. The analysis will also explore how costs vary with drug prices, organisation of the delivery of the integrated approach, and how cost‐effectiveness varies depending on the differences in the effectiveness and background prevalence of anaemia [9].

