##### Endpoints

The primary trial endpoint will be a change in Hb concentration, measured by HemoCue®, on the day of inclusion, and post‐intervention at the end of malaria transmission season, that is, 1 month after the last SMC cycle. The secondary endpoints will include incidence of clinical malaria, defined as fever of >37.5°C or a history of fever in the preceding 48 h, and a positive malaria blood film of any parasite density, detected by passive case detection during the surveillance period; change in prevalence of anaemia between the day of inclusion and post‐intervention at the end of malaria transmission season (anaemia will be defined as an Hb less than 11 g/dL); the incidence of solicited adverse events and adverse drug reactions assessed to be related to the study medications during a period of six consecutive days after administration of study drugs; prevalence and density of *Plasmodium falciparum* infection at the post‐intervention survey; prevalence and density of helminth infection; and prevalence and density of malaria‐helminth co‐infection at the post‐intervention survey. Tertiary endpoints will include the cost per child treated per year and the cost per anaemia case averted calculated by a cost analysis, and the incidence of anaemia among the children in the intervention and control arms will be used to estimate the incremental cost‐effectiveness of integrated SMC plus anthelminthic treatment versus SMC alone, in terms of incremental economic costs per DALY averted (Box 1).

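### The 80% power is for mean Hb level while the primary endpoint is change in Hb, and the only covariate list omits baseline Hb

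*Protocol article*

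**What the plan says.** Three sections of the protocol article describe the Hb comparison.

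- **Endpoints:** "The primary trial endpoint will be a change in Hb concentration", measured on the day of inclusion and one month after the last SMC cycle.
- **Introduction:** the hypothesis is about level, namely that "haemoglobin (Hb) concentration will be higher in the combined SMC‐MDA group than in the SMC alone group".
- **Sample size determination:** the calculation is also about level. Mean Hb with SMC alone "will be 10.5 g/dL with a standard deviation of 1.5 g/dL", and the study "will have 80% power to detect an increase in mean Hb of" 0.5 g/dL, with an intra-class correlation (ICC) of 0.05, 10 communities per arm and 60 children per community.

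The article's Statistical analysis plan section names chi-squared tests for adverse events, logistic models ("Logistic regressions with robust standard errors will be used to estimate odds ratios and 95% confidence intervals") and Poisson models for parasite intensities. Its one covariate list follows the logistic sentence and concerns a difference in odds "after controlling for baseline characteristics (sex, age group, weight and malaria and helminth" infection). Baseline Hb is not in it. The same section does use the pre-intervention parasite intensity as a covariate when post-intervention intensity is compared.

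**The concern.** The SD of a change score is not the SD of the level. It depends on how strongly a child's baseline and endline Hb are correlated, and the article gives neither that correlation nor an SD of change. The stated power therefore does not describe the declared endpoint unless the correlation happens to have one particular value.

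Baseline Hb is likely to be the best single predictor of endline Hb, and the primary endpoint already requires it to be measured. Yet the covariate list leaves it out, although the authors adjust parasite intensity for its own baseline. At stake is the precision of the primary comparison in a trial of 20 communities. It also matters that readers can tell which analysis the 80% refers to.

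**Working it through.** **Inputs from Sample size determination:** difference 0.5 g/dL, SD 1.5 g/dL, ICC 0.05, 60 children in each of 10 communities per arm, 5% level. The Statistical analysis plan section makes tests two-sided. No dropout allowance is stated and none is applied.

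**Assumptions:** r is not in the document, so a range is shown. The SD is taken as equal at baseline and endline. At first, r is taken as equal at child and community level.

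**Step 1. Reproduce the stated 80% for Hb level.**

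- Design effect = 1 + 59 × 0.05 = 3.95.
- SE = 1.5 × √(2 × 3.95/600) = 0.172 g/dL.
- Difference/SE = 0.5/0.172 = 2.905.
- Power = 82.8% (normal), or 78.4% (noncentral t, 2 × (10 − 1) = 18 df).

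The two values bracket 80%, so the figure stands for mean Hb at one time point.

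**Step 2. Change score and baseline-adjusted analysis.** Relative to the variance of the level, an unadjusted change has variance multiplied by 2(1 − r), and an analysis adjusted for baseline by 1 − r². The SE is 0.172 times the square root of the multiplier. Power is by t with 18 df.

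| r | Endline only | Change: multiplier, SE | Change: power | Adjusted: multiplier, SE | Adjusted: power |
|---|---|---|---|---|---|
| 0.3 | 78% | 1.40, 0.204 | 64% | 0.91, 0.164 | 82% |
| 0.4 | 78% | 1.20, 0.189 | 71% | 0.84, 0.158 | 85% |
| 0.5 | 78% | 1.00, 0.172 | 78% | 0.75, 0.149 | 89% |
| 0.6 | 78% | 0.80, 0.154 | 87% | 0.64, 0.138 | 93% |
| 0.7 | 78% | 0.60, 0.133 | 94% | 0.51, 0.123 | 97% |

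The change score matches the level when 2(1 − r) = 1, that is r = 0.5. It is worse below that and better above. The adjusted variance is never larger than either alternative: 1 − r² ≤ 1, and 1 − r² = (1 − r)(1 + r) ≤ 2(1 − r).

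**Step 3. Change with baseline as a covariate is the same analysis.** If endline − baseline = a + b·arm + c·baseline, then endline = a + b·arm + (c + 1)·baseline. The arm effect b and its SE are identical.

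**Step 4. Unequal correlation at the two levels.** The variance of a community mean is 0.05 × 2.25 = 0.1125 between communities plus 0.95 × 2.25/60 = 0.0356 within them. The between part is 0.1125/0.1481 = 76%, so the community-level correlation matters most. Take child-level r = 0.5 and one child-level slope of 0.5. The between part is then multiplied by 1 + 0.25 − 2 × 0.5 × (community-level r), and the within part by 0.75.

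- Community-level r = 0.3: SE = √(0.2 × (0.1125 × 0.95 + 0.0356 × 0.75)) = 0.163. Power is 82% adjusted and 67% for the change score.
- Community-level r = 0.9: power is 98% adjusted and 99% for the change score.
- Community-level r = 0.1: power is 76% adjusted, slightly under endline-only.

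**The case against.** The strongest reply is that the article never says the change will be analysed unadjusted. A reader might infer a raw change score, and from it that power is being thrown away. The document does not establish this. No Hb model is stated, and by step 3 a change endpoint with baseline as covariate loses nothing. The model may be in a separate analysis plan or full protocol that is not shown, so its absence from a condensed article is not in itself a fault. The covariate list belongs to the logistic models; it shows baseline Hb missing from the anaemia analysis, not from an Hb analysis. All of this stands.

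Three other strong readings also fail:

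- **Hb will be dichotomised.** Anaemia is a separate secondary endpoint, which the logistic model naturally serves.
- **The trial is underpowered.** The 80% reproduces on its own basis, and above r of about 0.5 a change score has more power than that.
- **Adjustment is needed to remove bias.** A valid cluster-level standard error already allows for chance imbalance between arms.

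The reply does not remove the mismatch between an endpoint stated as change and a power statement about level. Nor does it explain why the one list the authors chose to print leaves out baseline Hb when parasite intensity is adjusted for its own baseline.

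**Conclusion.** The point holds as one of consistency and efficiency. The stated 80% describes endline mean Hb. For an unadjusted change score, power would run from 64% at r = 0.3 to 94% at r = 0.7 and would equal the planned figure only near r = 0.5.

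Adjusting for baseline Hb gives 82% to 97% over the same range. Compared with an unadjusted change score, the gain is about 18 points at r = 0.3, 10 at r = 0.5 and 3 at r = 0.7. Compared with endline-only, it is about 4, 10 and 19 points.

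These figures rest on the planning values, an assumed r, equal SDs at both times, and r equal at child and community level. Under that last condition the adjusted analysis is never the weaker choice. If community-level r is lower, the gain over endline-only shrinks and can vanish. No shortfall in power and no bias is shown.

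**What to change.** 1. State the primary comparison as endline Hb between arms (or, equivalently, change in Hb) in a linear model that accounts for community and adjusts for each child's baseline Hb. Use a small-sample correction for 20 clusters, and report the effect in g/dL with a 95% confidence interval. A mixed model with a community random effect is one suitable choice.
2. Add baseline Hb to the covariate list for the anaemia model.
3. Identify baseline Hb as the value obtained before the first study drug. Table 1 marks sampling both at the pre-intervention survey and on Day 0.
4. State that the 80% refers to endline mean Hb. If change is kept as the basis, give the assumed SD of change or r.

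If a separate analysis plan already specifies item 1, it is enough to align the Endpoints and Sample size wording with it. The cost is wording only, with no new data and no change to recruitment. It should be settled before outcome data are seen, so that the choice among Hb analyses cannot depend on the results.
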